**Primary outcome**							
HbA1c level	Practice records	X				X	
**Secondary outcomes**							
*** Health-related outcomes***							
Probability to achieve the recommended glycaemic target	Practice records					X	
CV risk score	Practice records JJ risk engine	X		X		X	
HbA1c level	Practice records	X		X			
*** Behavioural outcomes***							
Behavioural management	SDSCA [53, 54]	X		X		X	
Prescribed medications	Practice record	X	X		X		X
**Psychosocial outcomes**							
Doctor-patient communication							
GP communication	GPAQ [55, 56]		X		X		X
Patient communication self-efficacy	AURA [57, 58]		X		X		X
Participatory decision-making	PACIC [59]	X					X
Psychosocial self-efficacy	ADS [60, 61]	X			X		X
Recall of CV risk score	Open-ended question		X	X			
Emotional response to CV risk score	Dedicated Likert scale [62]		X				
Perceived credibility of CV risk score	Dedicated Likert scale [63]		X				
Intentions to change behaviour	DLBQ [65]	X	X				

### Data collection

Eligible patients who agree to participate in the study following the face-to-face screening appointment will be notified of the start of the trial by the practice staff (i.e. once recruitment of all study participants is completed and all clusters are randomly allocated to intervention or control group). They will be informed that their next routine diabetes visit will be the baseline visit of the study.

On the day of the baseline visit, before seeing the GP, demographic information (age, sex, marital status, education level, employment status), diabetes-related characteristics (duration of T2DM, history of complications, current medications) and baseline measures will be collected using standardised forms or extracted from practice records by the practice staff. Baseline measures collected before the consultation include objective numeracy level assessed using the Japanese-language version of the Lipkus scale [66, 67] and relevant outcome measures described in Table 3. Right after the consultation, additional outcome measures will be collected (see Table 3).

The same procedure will apply at follow-up visits. The member of the practice staff in charge of data collection will make sure that the questionnaires are properly filled out and that no information is missing. Questionnaires will be linked to individual participants using practice and participant ID numbers that will preserve anonymity.

### Data analysis

#### Descriptive statistics

Participants will be described in terms of their baseline characteristics. Practice size (including both the total number of patients and the number of study participants) will also be reported. Continuous variables will be denoted using mean and standard deviation (normally-distributed variables) or median and interquartile range (non-normally distributed variables); while categorical variables will be denoted using count and percentage. Between-group differences in terms of participants’ characteristics and baseline measures will be tested using Student t tests and chi-square tests. In case significant between-group differences (*p*≤0.10) are observed, the relevant variables will be considered as potential confounders in further analysis.

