#### Secondary outcomes

##### Health-related outcomes

The probability to achieve the recommended glycaemic target (HbA1c <7.0% [53mmol/mol]) at 6 months in each group will be compared.The change in participants’ CV risk score (5-year CHD probability) will be evaluated at 3 and 6 months. Personalised CV risk scores will be calculated by the JJ risk engine based on participants’ personal characteristics and risk factors, including age, sex, body mass index, duration of T2DM, smoking status, HbA1c level (%), systolic blood pressure (mm Hg), HDL cholesterol (mg/dL), total cholesterol (mg/dL), and urine albumin creatinine ratio (mg/gCre). Systolic blood pressure will be measured at the GP practice by the standard method recommended by the Japanese Society of Hypertension [52].The change in HbA1c levels will also be evaluated at 3 months.

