#### Primary analyses for primary and secondary outcomes

The planned primary analyses will be carried out at the individual level, according to the intention-to-treat (ITT) principle. Between-group comparisons will be analysed using multilevel analysis to account for the dependency of observations. Between-group differences in the mean changes in primary and secondary outcomes will be estimated using linear mixed-effects models for continuous outcomes and logistic mixed-effects models for binary outcomes. Random effects will account for within-practice clustering and within-patient correlation. Fixed effects will be treatment group indicator (with the control group as the reference category), practice size (stratification variable) [68] and, where relevant, time indicators, their interaction effects, and baseline values of variables identified as potential confounders. In case normality assumptions are violated, outcome variables will be log-transformed and, if necessary, non-parametric tests will be used. Data analyses will be performed using Stata/MP 17 (StataCorp).

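### Patient-level baseline covariates, including baseline HbA1c, enter the outcome models only if a test that ignores clustering gives p ≤ 0.10, so the primary model is data-dependent and usually forgoes precision

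*Protocol article*

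**What the plan says.** Under Data analysis, Descriptive statistics, the Protocol article says that participants' characteristics and "baseline measures will be tested using Student t tests and chi-square tests". It continues: "In case significant between-group differences (*p*≤0.10) are observed", "the relevant variables will be considered as potential confounders in further analysis".

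Under Primary analyses for primary and secondary outcomes, the fixed effects are treatment group, practice size and, where relevant, time, interactions and "baseline values of variables identified as potential confounders". Practice size is unconditional because it is the stratification variable. On clustering, the same section states: "Random effects will account for within-practice clustering and within-patient correlation".

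Table 3 lists HbA1c as measured before the baseline visit, so it is one of the screened measures. No sentence makes it a covariate whatever the test shows. It does enter the primary outcome by subtraction, because that outcome is change in HbA1c at 6 months. The glycaemic-target outcome ("The probability to achieve the recommended glycaemic target (HbA1c <7.0% [53mmol/mol]) at 6 months in each group will be compared") falls under the same model description, in logistic form.

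**The concern.** There are three problems with the rule.

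- **The criterion.** Practices are randomised after patient recruitment is complete, so baseline differences between arms are due to chance. A small p-value then says nothing about whether a variable predicts 6-month HbA1c. The rule can bring in irrelevant variables and leave out the most obvious prognostic one.
- **The test.** Allocation is by practice, but the screening tests treat patients as independent. The outcome models allow for practices; the tests that choose their covariates do not. The threshold is therefore not a 10% test.
- **The model.** Which covariates the primary model contains is known only after looking at baseline data by arm.

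At stake are precision that the trial could have from data it already collects, and a primary estimate that depends on which side of a miscalibrated threshold each variable falls. For the target outcome there is no change score, so unless it is flagged, baseline HbA1c is not in that model at all.

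**Working it through.** **Inputs from the Sample size section:** difference 0.5%, SD 1.1% (not stated whether of change or of level), α 0.05, power 80%, ICC 0.035, mean cluster size 15 with SD 5, design effect 1.55, 119 per group, 10% loss, 264 in total, 20 practices. **Assumed:** the correlation ρ between baseline and 6-month HbA1c, which the document does not give.

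**1. The plan's own figures reproduce.** Two-sided, 2 × (1.96 + 0.842)² × 1.1² / 0.5² = 76 per arm (76.9 with the t distribution). The design effect is 1 + [(1 + 0.333²) × 15 − 1] × 0.035 = 1.548. Then 76.9 × 1.548 = 119 per group, and 238 / 0.9 = 264.

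**2. True rate of the 10% screen.** When the variance of the arm difference is inflated by a design effect DE that the test ignores, the chance of p ≤ 0.10 with no systematic difference is 2 × [1 − Φ(1.645/√DE)].

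| ICC | DE | Rate flagged |
|---|---|---|
| 0.02 | 1.313 | 15.1% |
| 0.032 | 1.501 | 18.0% |
| 0.035 | 1.548 | 18.6% |
| 0.047 | 1.736 | 21.2% |

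All four ICCs are quoted in the Sample size section. They are HbA1c values; other baseline variables may have other ICCs. In a simulation of 20 practices with 12 analysed patients each (238/20 = 11.9), baseline HbA1c was flagged in about 16% of trials. So it is left out as a covariate in roughly 81% to 84%.

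**3. Precision forgone.** Let k be the baseline SD divided by the 6-month SD. The variance of the baseline-adjusted estimate relative to the change score is (1 − ρ²) / (1 + k² − 2ρk). With k = 1 this reduces to (1 + ρ)/2.

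| ρ | k | Variance ratio |
|---|---|---|
| 0.5 | 1 | 0.75 |
| 0.7 | 1 | 0.85 |
| 0.8 | 1 | 0.90 |
| 0.5 | 0.8 | 0.75/0.84 = 0.89 |
| 0.7 | 0.8 | 0.51/0.52 = 0.98 |
| 0.7 | 0.7 | 0.51/0.51 = 1.00 |

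With k = 1 and 1.1% as the SD of change, a nominal 80% becomes about 90% (ρ 0.5) or 86% (ρ 0.7). Equivalently, 119 per group falls to about 90 (119 × 0.75 = 89.25) or 102 (119 × 0.85 = 101.15).

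**4. Power by strategy, simulated.** Same assumptions, ICC 0.035, true difference 0.5%. Simulation A: 20 practices of 12, practice-level t test, 6,000 runs per setting. Simulation B: unequal practice sizes, random-intercept models, 700 runs per setting.

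| Simulation | ρ | Change score | p ≤ 0.10 rule | Always adjusted |
|---|---|---|---|---|
| A | 0.5 | 81% | 83% | 90% |
| A | 0.7 | 81% | 82% | 87% |
| B | 0.5 | 75% | 77% | 85% |
| B | 0.6 | 78% | 81% | 86% |
| B | 0.7 | 75% | 77% | 83% |

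The rule costs 5 to 8 points against always adjusting. In A the standard error of the effect was 0.153 under the rule against 0.143 (ρ 0.5), and 0.159 against 0.153 (ρ 0.7).

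**5. Type I error under the rule** (simulation A, no effect): 3.8% at ρ 0.5 and 4.8% at ρ 0.7.

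**The case against.** Much of the case on the other side stands.

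- **Baseline is not ignored.** Practice size is always in the model, and baseline HbA1c is part of the change score. The model section, with patient random effects, time and interactions, could also be read as a longitudinal model with baseline as a response. This stands, and it means the point is narrower than a failure to use baseline. But subtracting baseline is not adjusting for it. An unconstrained group-by-time contrast does not recover the precision either, and the text does not set a common baseline mean.
- **The wording is soft.** Flagged variables are to be considered, and covariates enter where relevant, whereas the calculation assumes automatic entry. That is fair, but the discretion leaves the model less fixed, not more.
- **A reader might infer that the rule inflates false positives or underpowers the trial.** Neither is supported. Simulated type I error was below 5%. The sample size takes no credit for baseline adjustment, and the rule does slightly better than the plain change score in both simulations. Where simulated power falls below 80%, the unadjusted change score was already there (75%).
- **The gain is uncertain.** ρ, k and the meaning of the 1.1% are not documented. Entry at HbA1c ≥ 7.0% may narrow the baseline spread, and at k = 0.8 with ρ = 0.7 almost nothing is gained. This stands.
- **A reader might also link the rule to patients already below 7.0% at the baseline visit.** Eligibility uses the last routine check, so this can happen, but it follows from eligibility timing. The screening rule does not cause it.
- **The analysis plan is not shown.** That would excuse a missing covariate list. It does not excuse a selection rule that the article itself states.

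**Conclusion.** The point holds as an efficiency and pre-specification fault. Patient-level covariates are chosen by a criterion that does not identify prognostic variables, using tests that flag about 18.6% of chance imbalances at the protocol's own design effect, or about 15% to 21% over the ICCs it quotes. Baseline HbA1c is consequently left out as a covariate in most realisations.

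The cost against always adjusting is roughly 5 to 8 points of power. That figure assumes ρ between 0.5 and 0.7, equal variances at baseline and 6 months, and 1.1% as the SD of change; it shrinks towards zero if the baseline SD is well below the 6-month SD. The criticism of the criterion and of the unclustered tests depends on none of these three assumptions. The validity of the trial's error rate and its planned 80% power are not called into question by this rule.

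**What to change.** - Delete the between-arm baseline significance tests and the p ≤ 0.10 rule. Describe baseline balance by arm without p-values.
- Pre-specify baseline HbA1c, together with practice size, as fixed covariates in the primary model. A longitudinal model with a common baseline mean for the two arms is an acceptable alternative.
- Put continuous baseline HbA1c in the logistic model for the < 7.0% target.
- Name any further covariates in advance, on prognostic grounds.

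This is a change of wording in the analysis section or the analysis plan, to be made before the final analysis. It needs no new data, since HbA1c is already measured at baseline, and no change to the sample size.

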#### Primary analyses for primary and secondary outcomes

The planned primary analyses will be carried out at the individual level, according to the intention-to-treat (ITT) principle. Between-group comparisons will be analysed using multilevel analysis to account for the dependency of observations. Between-group differences in the mean changes in primary and secondary outcomes will be estimated using linear mixed-effects models for continuous outcomes and logistic mixed-effects models for binary outcomes. Random effects will account for within-practice clustering and within-patient correlation. Fixed effects will be treatment group indicator (with the control group as the reference category), practice size (stratification variable) [68] and, where relevant, time indicators, their interaction effects, and baseline values of variables identified as potential confounders. In case normality assumptions are violated, outcome variables will be log-transformed and, if necessary, non-parametric tests will be used. Data analyses will be performed using Stata/MP 17 (StataCorp).

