### Sample size

Assuming individual randomisation, recruitment of at least 76 participants per arm would be required to achieve 80% power with type I error α=0.05. These calculations have assumed the detection of a clinically meaningful difference of 0.5% (5.5 mmol/mol) in change in HbA1c between the two arms [71] and standard deviation of 1.1% (12 mmol/mol) based on a previous study with comparable population [72]. However, this sample size needs to be inflated to account for clustering effects and potential dropouts. Therefore, the final sample size will be adjusted according to the final number of clusters, the cluster average size, the estimated intra-class correlation coefficient (ICC), and the expected drop-out rate.

A systematic search of ICCs used in the design of cluster RCTs in T2DM with HbA1c as primary (continuous) outcome found that the median value used in published trials was 0.047 [73]. However, recent studies investigating the actual ICCs from large primary care datasets reported values comprised between 0.02 and 0.032 for HbA1c [74], suggesting that ICCs used in sample size calculation for cluster RCTs tend to be over conservative. Assuming an ICC of 0.035 and accounting for potential variations in cluster size, the effective sample size required to detect a 0.5% difference in HbA1c and to achieve 80% power with type I error α=0.05 is 119 participants per group. These calculations have assumed the mean cluster size to be 15 with standard deviation of 5, yielding a coefficient of variation of 0.33 and a design effect of 1.55 [75]. Moreover, assuming 10% loss to follow-up, 264 participants in total will be needed.

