Based on these calculations, we aim to enrol 20 practices in the study. After 10 practices are enrolled (the inclusion of a minimum of 10 clusters is recommended, otherwise it is difficult to maintain both an appropriate type I error and sufficient power, even when small-sample correction methods are applied [76]), each practice will proceed with the recruitment of eligible patients. Two months after the start of the recruitment process, we will carry out a first assessment of each cluster size, calculate the coefficient of variation, and determine whether the total number of enrolled participants is sufficient according to the updated sample size calculation. Should this number be too small in view of the required sample size, we will recruit additional clusters until an effective sample size is reached, as long as our budget constraints permit it. In the unlikely event that additional practices cannot be recruited, or that the coefficient of variation in cluster size turns out to be much higher than expected (making the effective sample size too big given our budget constraint), we will consider opting for a cluster design with providers, rather than practices, as the unit of randomisation.

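### The sample size and its re-check make no allowance for the small number of practices: about 75% power on the calculation's own inputs, about 79% at the 20-practice target

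*Protocol article*

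**What the plan says.** The Sample size section of the protocol article starts from individual randomisation: "recruitment of at least 76 participants per arm would be required". The inputs are a "clinically meaningful difference of 0.5% (5.5 mmol/mol) in change in HbA1c between the two arms" and a "standard deviation of 1.1% (12 mmol/mol) based on a previous study with comparable population". For clustering it continues: "Assuming an ICC of 0.035 and accounting for potential variations in cluster size", 119 participants per group are needed to "achieve 80% power with type I error α=0.05". On cluster size: "These calculations have assumed the mean cluster size to be 15 with standard deviation of 5", which gives a coefficient of variation of 0.33 and a design effect of 1.55. With 10% loss to follow-up the total is 264.

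The same section aims for 20 practices but lets patient recruitment begin once 10 have joined. Two months later the team re-runs the calculation with the observed cluster sizes. It adds practices if the number is too small and the budget allows. Ten is justified as a recommended minimum, below which "it is difficult to maintain both an appropriate type I error and sufficient power, even when small-sample correction methods are applied".

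The section on primary analyses specifies linear mixed models for continuous outcomes, with practice size as a fixed effect, in Stata/MP 17: "Random effects will account for within-practice clustering and within-patient correlation". It names no degrees-of-freedom method, no reference distribution and no choice between ML and REML.

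**The concern.** Whole practices are allocated, so the treatment effect is estimated from differences between practices. The relevant degrees of freedom are then about the number of practices minus 2: 18 with 20 practices, 14 with 16 and 8 with 10. A design effect corrects the variance for clustering, but it does not correct for having few clusters from which to estimate that variance. A calculation with normal quantiles therefore overstates power, and more so the fewer the practices.

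Two things are at stake. The stated 80% is somewhat too high. And the two-month re-check decides whether more practices are needed: if it uses the same formula, it can report enough patients when power is well short of 80%.

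**Working it through.** **Inputs, all from the Sample size section:** difference 0.5, SD 1.1, α 0.05, power 80%, ICC 0.035, mean cluster size m = 15, CV 0.33, loss 10%, 20 practices planned, recruitment starting at 10. Sidedness is not stated; two-sided is assumed because it reproduces the plan's figure.

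**Reproducing the plan.**
- n per arm = 2 × (1.96 + 0.8416)² × 1.1² / 0.5² = 75.98, so 76. (A t formula at the individual level gives 77.)
- Design effect = 1 + ((CV² + 1) × m − 1) × ICC = 1 + ((0.333² + 1) × 15 − 1) × 0.035 = 1.548.
- 76 × 1.548 = 117.7 and 77 × 1.548 = 119.2, against 119 stated.
- 119 / 0.9 = 132.2; 2 × 132 = 264.

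All four figures reproduce within rounding, and no term contains cluster-level degrees of freedom.

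**Power on the calculation's own inputs.** 238 analysed / 15 ≈ 16 practices. SE = √(2 × 1.1² × 1.548 / 119) = 0.1774, and noncentrality = 0.5 / 0.1774 = 2.82. Against z (critical value 1.960) power is about 80.4%. Against t on 14 df (critical value 2.145) it is 74.6%.

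**Power for 238 analysed (264 enrolled), by number of practices, ICC 0.035.** Here m = 238 / practices and CV stays at 0.33.

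| Practices | m | Design effect | Power, z | Power, t on (practices − 2) df |
|---|---|---|---|---|
| 20 | 11.9 | 1.43 | 83.5% | 79.2% |
| 18 | 13.2 | 1.48 | 82.2% | 77.2% |
| 16 | 14.9 | 1.54 | 80.6% | 74.7% |
| 10 | 23.8 | 1.89 | 72.2% | 61.0% |

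With 20 practices, the t-based power is 84.4% at ICC 0.02, 80.3% at 0.032 and 75.3% at 0.047. The section itself cites all three ICC values.

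**Re-check, if it repeats the formula.** Solving N = 2 × 75.98 × design effect(N / practices) gives the analysed N at which the formula is just met. By construction the z power there is 80%.

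| Practices | Analysed N | Mean size | Power, t |
|---|---|---|---|
| 10 | about 358 | 35.8 | 69.0% |
| 16 | about 233 | 14.5 | 74.1% |
| 20 | about 208 | 10.4 | 75.5% |

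**Type I error, only if an uncorrected Wald z were used.** This was simulated with 8,000 null trials per setting: a random practice intercept, ICC 0.035, 238 analysed, size CV 0.33, allocation in size-ordered pairs and practice size as a covariate. Rejection rates were 6.0% (REML) to 7.5% (ML) with 20 practices, and 7.5% to 10.9% with 10. With REML and a t reference they were about 4.4% and 3.6%.

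**The case against.** Several points count against a harsher reading, and most of them stand.

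- A reader might infer that the primary model uses z inference and so loses the 5% error rate. The article does not say so. It is silent on the reference distribution, and such a detail is commonly left to an analysis plan, which is not shown.
- A reader might take the remark about small-sample corrections as an admission about this trial. In context it describes what happens below 10 clusters, and the plan targets 20.
- A reader might conclude that the re-check ignores the number of practices. The Sample size section lists the final number of clusters among the quantities that will adjust the sample size. What can be shown is narrower: the one worked formula has no allowance for cluster-level degrees of freedom, and no other formula is given for the re-check.
- A reader might conclude that the planned trial misses its power. At 20 practices and 264 patients the shortfall is under one point, because 264 / 20 = 13.2 enrolled per practice gives a smaller design effect than the assumed 1.55. The ICC of 0.035 also exceeds the observed values of 0.02 to 0.032 that the section cites.
- Ten practices is where patient recruitment starts, not the intended final number. Just meeting the formula there needs about 36 analysed per practice, far above the assumed mean of 15. The plan also allows extra practices or randomisation by provider.
- The power formula and the simulation use a single change score without baseline HbA1c. The planned model may do better.

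What remains is that the worked calculation falls short of 80% on its own inputs. Nothing in the text stops the re-check from carrying that shortfall forward, and it does so even at 16 or 20 practices if enrolment only just meets the formula.

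**Conclusion.** The point holds in a limited form. The calculation behind 119 per group omits the small-cluster allowance. It delivers about 75% power at the roughly 16 practices that its own cluster size implies, and about 79% at the stated target of 20 practices and 264 enrolled. The planned design is therefore close to adequate. The exposure is a trial that proceeds with fewer practices, or one that stops adding practices once the formula is just met (69% to 75.5% for 10 to 20 practices). Inflated type I error is conditional on an analysis option that the article neither states nor excludes.

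These figures assume a two-sided α, an SD of 1.1 for the total variance of the change, a CV of 0.33 at every mean size, exactly 10% loss, and (practices − 2) degrees of freedom. ICC is the most influential assumption: over 0.02 to 0.047, power at the target runs from about 84% to 75%.

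**What to change.** In the Sample size section, replace the normal quantiles by t quantiles on (practices − 2) df, and state that the two-month re-check uses the same t-based formula with the actual number of practices. Restate power by number of practices: about 79% with 20 practices and 264 patients, about 75% with 16. In the section on primary analyses, state that the primary linear mixed model is fitted by REML with Kenward-Roger or Satterthwaite degrees of freedom.

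The cost is wording and a software option. The stated power becomes slightly lower, and the confidence interval slightly wider than a z interval with the same standard error: by 2.101 / 1.960, or about 7%, with 20 practices. No extra patients are needed at the target if about 79% is accepted. Reaching a full 80% would take about 274 enrolled with 20 practices, or about 332 with 16.

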### Outcomes

#### Primary outcome

The primary outcome will be the change in HbA1c levels at 6 months in the FEEDBACK intervention group compared with the control group. HbA1c levels will be derived from the samples collected by venepuncture at baseline, 3 months, and 6 months, obtained by the NGSP (National Glycohaemoglobin Standardisation Programme) certified method.

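### If a patient random intercept alone carries within-patient correlation across three HbA1c visits, the standard error of the 6-month contrast can be too small; an unstructured visit covariance removes the risk

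*Protocol article*

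**What the plan says.** All places are in the protocol article.

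- **Primary outcome:** "The primary outcome will be the change in HbA1c levels at 6 months in the FEEDBACK intervention group compared with the control group". The same paragraph adds that "HbA1c levels will be derived from the samples collected by venepuncture at baseline, 3 months, and 6 months".
- **Health-related outcomes** (secondary): "The change in HbA1c levels will also be evaluated at 3 months".
- **Primary analyses for primary and secondary outcomes:** effects are "estimated using linear mixed-effects models for continuous outcomes and logistic mixed-effects models for binary outcomes". On dependence: "Random effects will account for within-practice clustering and within-patient correlation". The fixed effects are treatment group, practice size and "where relevant, time indicators, their interaction effects, and baseline values of variables identified as potential confounders".
- **Table 3:** the primary-outcome row marks HbA1c before the baseline and 6-month visits only. The 3-month value has its own row among the secondary outcomes.
- **Sensitivity analyses:** the primary approach is said to be unbiased when data are missing at random.

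No residual covariance structure, visit-specific variance or robust standard error is named. No between-visit correlation and no standard deviation for 3-month change is given.

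**The concern.** A patient random intercept with independent residuals imposes one variance at every visit and one correlation between every pair of visits. The implied variance of a change score is then the same for any two visits, and it is estimated by pooling all of them. The primary result concerns one pair, baseline and 6 months. If measurements 3 months apart are more alike than measurements 6 months apart, the pooled variance lies below the variance of the 6-month change. The confidence interval for the primary contrast is then too narrow and its type I error exceeds the stated 5%.

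This is a patient-level matter. It appears even with no variation between practices, and a correct practice-level term does not cure it. The same sentence governs the other scores that Table 3 schedules at three visits, such as CV risk score, SDSCA and ADS.

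**Working it through.** **1. The plan's own figures.** The Sample size section reproduces and is not affected.
- Per arm, individual randomisation: 2 × (1.96 + 0.8416)² × 1.1² / 0.5² = 75.98, so 76, in line with "recruitment of at least 76 participants per arm would be required to achieve 80% power with type I error α=0.05".
- Design effect: 1 + [(1 + 0.333²) × 15 − 1] × 0.035 = 1.548 (stated 1.55).
- Clustered: 76 × 1.548 = 117.7, or 77 × 1.548 = 119.2 with the t-based 77 (stated 119).
- With 10% loss: 2 × 119 / 0.9 = 264.4 (stated 264).

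**2. Formulas for a patient random intercept only.** Complete data, group-by-visit means, no practice variance, unit variance at each visit. Correlations are r03, r36 and r06.
- Levels at three visits: model variance of a change = 2 × (1 − mean of r03, r36, r06).
- Changes at two follow-ups: model variance = [2(1 − r03) + 2(1 − r06)] / 2.
- True variance of the 6-month change = 2(1 − r06).
- SE ratio = √(model / true). Type I error = 2 × [1 − Φ(1.96 × ratio)].

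**3. Results.** The correlations are assumptions, because the article gives none.

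| r03 / r36 / r06 | Change: ratio, type I | Level: ratio, type I |
|---|---|---|
| 0.6 / 0.6 / 0.6 | 1.00, 5.0% | 1.00, 5.0% |
| 0.7 / 0.7 / 0.6 | √(0.70/0.80) = 0.935, 6.7% | √(0.333/0.40) = 0.913, 7.4% |
| 0.7 / 0.7 / 0.49 | √(0.81/1.02) = 0.891, 8.1% | √(0.37/0.51) = 0.852, 9.5% |
| 0.8 / 0.8 / 0.64 | √(0.56/0.72) = 0.882, 8.4% | √(0.253/0.36) = 0.839, 10.0% |

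In 8,000 simulated trials of 119 per arm, the last three rows gave 6.4%, 8.8% and 8.8% (change) and 7.1%, 10.4% and 10.6% (level). Using the 6-month change's own variance gave 5.1–5.3%.

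**4. The same on the HbA1c scale, showing both directions.** Take the Sample size section's 1.1% as the SD of 6-month change, and give the 0–3 and 3–6 month changes a common assumed SD s. For levels, ratio = √[(2s² + 1.21)/3] / 1.1.

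| s | Ratio | Type I error |
|---|---|---|
| 1.1 | 1.00 | 5.0% |
| 1.0 | 0.94 | 6.5% |
| 0.9 | 0.88 | 8.4% |
| 0.8 | 0.83 | 10.5% |
| 1.2 | 1.06 | 3.8% |

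A simulation with 20,000 replicates and 130 per arm gave 5.0%, 6.5%, 8.4%, 10.4% and 4.0% for these rows. With the 6-month change's own variance it gave 4.9–5.3% in every case.

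**5. Readings under which the standard error is not understated.**
- *Baseline and 6 months only:* with two visits the random-intercept variance of the change is 2 × [(V0 + V6)/2 − Cov] = V0 + V6 − 2Cov, which is the true value.
- *One 6-month change per patient:* nothing is pooled.
- *Random intercept plus slope on three levels:* let V03, V36 and V06 be the change variances. Matching the model to complete data gives residual variance (2·V03 + 2·V36 − V06)/6 and slope variance per 3-month step (2·V06 − V03 − V36)/6. The implied variance of the 6-month change is 4 × slope + 2 × residual = (6/6)·V06 = V06, whenever the slope variance is not negative. Every row of the table in step 3 then has ratio 1.00. If V06 is below the mean of V03 and V36, the slope variance stops at zero and the too-large standard error of the random-intercept model returns.

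**The case against.** The strongest objection is that the plan does not state the model that produces these error rates. The plural term random effects covers an intercept plus a slope as readily as an intercept alone, and step 5 shows that the slope removes the understatement in every scenario. That stands, and it makes the point conditional.

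Second, pooling three visits for the primary test is implied, not stated. The time terms enter only where relevant, and Table 3's primary row lists two visits. This also stands. Three visits remain the more natural reading: the Primary outcome paragraph lists three samples, the model includes "time indicators, their interaction effects", a patient random effect needs repeated values per patient, and the missing-at-random claim fits a longitudinal model. None of this settles it.

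Third, the direction of error is not fixed by the documents. A reader might infer that the 6-month standard error will be too small. With no visit correlations or 3-month SD given, it may be right (constant correlation) or too large (shorter-interval changes more variable). Remarks elsewhere in the article, that behavioural change may take longer to show in HbA1c and that goals are revised at 3 months, make decay plausible but give no figure.

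Fourth, covariance structure is commonly left to an analysis plan, and this is a condensed article. That limits the weight of the point. It does not remove it, because the article does name the device for within-patient correlation, and its simplest form can fail.

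**Conclusion.** The point holds as a conditional weakness. If the primary model pools the three HbA1c visits with a patient random intercept only, and correlation decays as assumed here, the 6-month standard error is about 6–16% too small and type I error is about 6.7–10%. This rests on assumed correlations, complete data and no practice variance. Under constant correlation there is no error, and if shorter-interval changes vary more the test is conservative.

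The documents do not support saying that the planned interval will be too narrow, or that the plan has fixed a wrong covariance. The recommendation does not depend on which reading is right, because an unstructured covariance gives the 6-month change its own variance under every pattern considered. A random slope does so only when the 6-month change varies at least as much as the shorter changes do on average. This is a cheap improvement.

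**What to change.** In the section on primary analyses for primary and secondary outcomes, for continuous outcomes measured at three visits, replace the patient random effect with an unstructured within-patient residual covariance across visits (a separate variance per visit and a separate covariance per pair). Keep the practice-level random terms. State that the primary test is the treatment contrast at 6 months from this model.

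The cost is one sentence and one residual-structure option in Stata's mixed command. For levels at three visits the patient-level covariance has 3 variances + 3 covariances = 6 parameters instead of 2 (intercept and residual), so four more, for about 264 patients. If correlation does decay, the interval becomes slightly wider. Recruitment, visits and sample size do not change.
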